# The effect of co supplementation of omega-3 and vitamin D on cardio metabolic risk factors and psychological distress in reproductive-aged women with prediabetes and hypovitaminosis D: a study protocol for a randomized controlled trial

**DOI:** 10.1186/s13063-019-3948-5

**Published:** 2019-12-30

**Keywords:** Vitamin D, Omega-3 fatty acids, Docosahexaenoic acid, Eicosapentaenoic acid, Insulin resistance, Prediabetic state, Type 2 diabetes mellitus

## Abstract

**Background:**

A prediabetic state is a risk factor for type 2 diabetes. There are no approved drugs to manage prediabetes. Among the supplements routinely used by individuals, vitamin D and omega-3 have been studied to reduce fasting blood sugar. However, their co-supplementation has not been studied in individuals with prediabetes. This randomized controlled trial is designed to determine the effects of these two supplements on fasting blood sugar, other cardio metabolic risk factors, and psychological distress in reproductive-aged women with prediabetes and hypovitaminosis D.

**Methods/design:**

This 2 × 2 factorial, triple-blind, randomized, placebo-controlled, clinical trial will be done on 168 women of reproductive age diagnosed with prediabetes and hypovitaminosis D. Participants will be randomly assigned equally to four groups: (1) 1000 mg omega-3 fatty acid twice a day + vitamin D placebo every two weeks; (2) omega-3 fatty acid placebo twice a day + 50,000 IU vitamin D every two weeks; (3) 1000 mg omega-3 fatty acid twice a day + 50,000 IU vitamin D every two weeks; (4) omega-3 fatty acid placebo twice a day + vitamin D placebo every two weeks for eight weeks. At the beginning, participants will provide a self-reported questionnaire on the sociodemographic characteristics. At baseline and post-intervention visits, physical activity, Depression Anxiety Stress Scale 21 and Pittsburgh Sleep Quality Index, and a three-day food record will be collected for each individual. Blood pressure, weight, height, and waist circumference will also be measured.

At the beginning and at the end, a blood sample will be used for estimating serum glucose indices (fasting blood sugar and insulin, homeostasis model assessment-insulin resistance, homeostasis model assessment-beta cell function), lipids (triglyceride, low-density lipoprotein cholesterol, high-density lipoprotein cholesterol, total cholesterol), and vitamin D status.

Data analysis using Kolmogorov–Smirnov test, paired t-test, one-way analysis of variance, and repeated measures analysis of variance will be conducted through SPSS-24 software.

**Discussion:**

The primary aim of the present trial is to determine the effect of vitamin D and/or omega-3 on glycemic indices, lipid profiles, psychological distress, blood pressure, and anthropometric indices in prediabetic women with hypovitaminosis D. The results from this trial will provide evidence on the efficacy of these two supplements for preventing or delaying the onset of type 2 diabetes in high-risk individuals.

**Trial registration:**

Iran Clinical Trials Registry, IRCT20100130003226N17. Registered on 9 February 2019.

## Background

Diabetes mellitus (DM) is a common chronic disease. There has been a threefold increase in the prevalence of diabetes between 1980 and 2014 [1]. In 2017, prevalence of diabetes has been reported as 8.51% in the world and 9.6% in Iran [2]. Control of risk factors is one of the suggestions for the prevention of non-communicable diseases [3]. Prediabetes is a risk factor of diabetes mellitus and is typically defined as having either impaired glucose tolerance (IGT) or impaired fasting glucose (IFG) or both [4]. According to the International Diabetes Federation, the number of adults with prediabetes is expected to increase worldwide, to 471 million by 2035. Each year, about 5%–10% of individuals with prediabetes will progress to diabetes [5]. Prediabetes may have adverse effects on end organs, such as blood vessels, the heart, eyes, and kidneys [6].

Reproductive health in women is affected by insulin resistance. It causes depressive and fertility disorders, urinary incontinence, vaginal and urinary tract infections, menstrual changes, and sexual dysfunction and has also been linked to an increased risk of cancer of the breast and ovaries [7].

In addition, evidence suggests that psychological distress, including depression, anxiety, or stressful experiences, might affect diabetes, in terms of both its onset and its exacerbation [8]. Moreover, studies have shown that both decreased quantity and quality of sleep are associated with diabetes [9].

On the other hand, several studies have found that weight loss and increase in physical activity improved sensitivity to insulin [10, 11]. However, maintaining weight and physical activity over long periods of time is very difficult. Therefore, they are inadequate to reduce the risk of progression to diabetes [12].

As prediabetes is not known as a disease, there are currently no approved drugs to manage it.

Considering the above reasons, it is necessary to find safe and effective interventions to control prediabetes [13]. Keeping in mind that one of the suggested pathological mechanisms in the development of diabetes is subclinical inflammation, it seems that anti-inflammatory agents such as omega-3 may delay the risk of the development of diabetes in people with prediabetes [14–16].

Moreover, the results of several studies show an association of vitamin D deficiency with insulin resistance, impaired insulin secretion, and their important metabolic consequences [17–19]. In addition, a meta-analysis has declared that depression is associated with a lower level of vitamin D [20]. Further, effectiveness of omega-3 on depression has been shown in another meta-analysis [21].

In some studies, it could be seen that combined high-dose omega-3 fatty acids and high-dose vitamin D therapy improved glycemic indices in patients with new onset type 1 diabetes mellitus and women with gestational diabetes (GDM) [22, 23]. Since the effect of co-supplementation of vitamin D and omega-3 on fasting blood sugar and other cardiometabolic risk factors are not well documented, this study has been designed to evaluate the complementary or synergistic effects of vitamin D and omega-3 on fasting blood sugar and other glycemic indices, serum lipids, and psychological distress in reproductive-aged women with prediabetes and hypovitaminosis D.

## Methods/design

### Study design

This is an eight-week 2 × 2 factorial, triple-blinded (study investigators, participants, and statistical analyzer), randomized, placebo-controlled trial. Overall, 168 women of reproductive age diagnosed with prediabetes (fasting glucose 100–125 mg/mL) will be screened for enrolment in the study. This study will be conducted at Shahid Rastravesh Health Center Laboratory, Alborz University of Medical Sciences, Karaj, Iran.

Eligible participants who meet the inclusion and exclusion criteria will be randomly divided into four groups to receive double placebo (omega-3 and vitamin D placebos), omega-3 placebo and vitamin D supplement, omega-3 supplement and vitamin D placebo, and supplements of omega-3 and vitamin D.

In this factorial 2 × 2 design, we want to address five questions:
Compared to placebo, is omega-3 effective?Compared to placebo, is vitamin D effective?Are vitamin D + omega-3 more effective than placebo?Are vitamin D + omega-3 more effective than vitamin D alone?Are vitamin D + omega-3 more effective than omega-3 alone [24]?

Participants will visit the trial sites three times: at baseline (0 weeks); after three days; and post intervention (eight weeks after intervention). The flow chart of the study protocol is presented in Fig. 1.

**Fig. 1 Fig1:**
[figure not shown]
Trial protocol *flow chart*

### Objectives

Compare the mean serum lipid (triglycerides [TG], total cholesterol [TC], low-density lipoprotein cholesterol [LDL-C], high-density lipoprotein cholesterol [HDL-C]) and glucose indices (fasting blood sugar [FBS], fasting blood insulin [FBI], homeostasis model assessment - insulin resistance [HOMA-IR], homeostasis model assessment - beta cell function [HOMA-B]) between the four groups and within each group, before and after intervention.Compare the means of anthropometric indices (weight, waist circumference, body mass index [BMI]) and systolic and diastolic blood pressures between the four groups and within each group, before and after the intervention.Compare the mean scores of the Depression Anxiety Stress Scale (DASS-21) and Pittsburgh Sleep Quality Index (PSQI) between the four groups and within each group, before and after intervention.Determine the relationship between changes in mean level of serum vitamin D and each of the glucose indices, serum lipids, and the mean scores of the DASS-21 and PSQI between the four groups and within each group, during intervention.

### Inclusion criteria

Women of reproductive age (aged 15–50 years);FBS 100–125 mg/mL [1, 2, 25];Vitamin D < 32 ng/mL [26];BMI < 30 kg/m^2^.

### Exclusion criteria

Diagnosed pathological conditions such as thyroid or parathyroid disorders, PCO, seizures, liver or kidney disease, neurological disorders, cancer, cardiovascular disease, type 1 or 2 diabetes, sarcoidosis, or other granulomatous disorder;Intake of vitamin D or omega-3 during the last six months;Breastfeeding, pregnant, and/or planning for pregnancy in the next two months;Intake of drugs that interact with omega-3 (including aspirin or anticoagulants [warfarin, heparin]) or with vitamin D (such as cardiac glycosides, cholestyramine, anticonvulsant drugs or thiazides);Taking herbal or chemical drugs that affect serum lipids or blood glucose level;In case of taking prescribed supplements different from study protocol.

### Study participants

Women of reproductive age with prediabetes from Karaj health centers diagnosed with FBS test (fasting glucose 100–125 mg/mL) [1, 25] will be invited to this study.

The study investigator will call participants by phone and will screen them according to the inclusion and exclusion criteria.

Eligible participants will be referred to the Shahid Rastravesh Health Center. First, the goals, methods, and benefits of the intervention will be explained by the investigator and the informed consent form will be signed by participants. At the beginning, 10 mL of blood will be taken from a peripheral vein after a 12-h overnight fast to assess plasma glucose levels, insulin, TG, HDL-C, TC, and vitamin D. After centrifuging for 10 min (3000 rpm), the serum samples will be frozen simultaneously and stored at − 80 °C until analyzed [12]. LDL-C will be estimated based on the Friedewald equation [27]. Participants will receive a three-day food record. The investigator will explain how to complete the form to each participant.

After three days, women who have been confirmed as having prediabetes (fasting glucose 100–125 mg/mL) and hypovitaminosis D (vitamin D < 32 ng/mL) [26] will be invited to the Shahid Rastravesh Health Center.

The sociodemographic characteristics questionnaire, short-form International Physical Activity Questionnaire (IPAQ), DASS-21, and PSQI will be completed with interviews. The investigator will review completed three-day food record in presence of each participant.

Anthropometry including weight, height, and waist circumference will be measured using a digital scale, stadiometer, and non-elastic tape, respectively.

Blood pressure (systolic and diastolic) will also be measured with a digital manometer.

All the above-mentioned stages, including blood sampling, completing four questionnaires (three-day food record, IPAQ, DASS-21, and PSQI), anthropometric measurements and measuring blood pressure, will be repeated after eight weeks.

At the end, the evaluated outcomes will be presented to participants privately. A Data Monitoring Committee (DMC) will also monitor during and at the end of this study (Fig. 2).

**Fig. 2 Fig2:**
[figure not shown]
Contents of the schedule of enrolment, interventions, and assessments

### Sample size

Sample size was estimated according to previous study using the following formula [22]:
$$ n=\frac{{\left(\kern0.28em {Z}_{1-a/2}+{Z}_{1-\beta}\kern0.28em \right)}^2\kern0.28em \left(\kern0.28em {S}_1^2+{S}_2^2\kern0.28em \right)}{{\left({\mu}_1-{\mu}_2\right)}^2} $$

Based on a study by Jamilian et al. [22], the mean ± standard deviation [SD]) of FBS in co-supplementation of vitamin D and omega-3 and placebo groups were considered as 86.8 ± 6.40 and 94.6 ± 10.30, respectively. Given the type I and II error by 5% and 20%, respectively, the calculated sample size was 20 in each group. Since we want to perform five pairwise comparisons between the study groups, the sample size was increased to 38 individuals in each group for multiple adjustment. By considering four groups and an attrition rate of 10%, the estimated sample size was 168 individuals [24].

To achieve the target sample size, all invited patients who will come the Shahid Rastravesh Health Center will be included if they are willing to participate in the study (considering the inclusion criteria of the study).

Finally, a total number of 168 women will be allocated equally to four groups using the stratified permuted block randomization method.

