
### Statistical analysis

The effect of the intervention on all participants will be assessed based on intention-to-treat and per-protocol analyses. The data will be checked for plausibility by randomly checking the accuracy and completeness and source data verification. The normality of continuous variables will be determined using a Kolmogorov–Smirnov test. Appropriate statistical transformation (logarithmic transformation, square root transformation, cube root transformation, or reciprocal transformation) will be used for continuous variables with not normal distribution.

Hence, statistical analysis for continuous variables with normal distribution (parametric tests) will be used in this study.

Continuous variables with normal distribution and transformed variables will be expressed as mean ± SD. Categorical data will be presented as frequency (percentage).

To compare the mean differences within each group, before and after intervention, the paired t-test will be used for continuous variables.

For continuous variables, one-way analysis of variance (ANOVA) will be used to detect differences in sociodemographic characteristics, metabolic profiles, physical activity levels, and dietary intakes at the study baseline between the four groups.

Categorical data at the study baseline will be analyzed using the Chi-squared test between the intervention groups.

Repeated measures analysis of variance (RM ANOVA) with Bonferroni procedure to adjust for the five comparisons will be used to assess time effects and time-by-treatment (vitamin D and/or omega-3) interaction effects on all outcome variables between groups.

Since we have multiple endpoints and we will compare five pairwise comparison, all *p* values will be corrected using the Bonferroni adjustment method.

Two-way RM ANOVA with Bonferroni adjustment for comparisons will be used to assess the relationship between changes in mean serum vitamin D level and each of fasting blood sugar and other outcome variables between groups.

Levenes test for independent data in one-way ANOVA and Mauchly’s test in RM ANOVA will be used to test homoscedasticity.

All statistical measurements will be reported with 95% confidence intervals (CI). A *p* value < 0.05 will be considered statistically significant. All statistical analyses will be performed using SPSS version 24.

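### The 38 per group given as the size for five pairwise comparisons rests on one contrast, does not follow from the stated formula (29 does), and leaves at least two comparisons weakly powered if each single agent falls between placebo and combination

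*Protocol article*

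**What the plan says.** The Study design section announces "In this factorial 2 × 2 design, we want to address five questions". The questions are each single agent against placebo (for example "Compared to placebo, is omega-3 effective"), the combination against placebo, and the combination against each single agent (for example "Are vitamin D + omega-3 more effective than vitamin D alone").

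The Sample size section gives planning values for one of these contrasts only: fasting blood sugar in the "co-supplementation of vitamin D and omega-3 and placebo groups were considered as 86.8 ± 6.40 and 94.6 ± 10.30". From these it reports: "Given the type I and II error by 5% and 20%, respectively, the calculated sample size was 20 in each group". The next step is "Since we want to perform five pairwise comparisons between the study groups, the sample size was increased to 38 individuals in each group", with multiplicity as the reason. Neither the adjusted alpha nor a difference for the other four comparisons is given. After 10% attrition, "a total number of 168 women will be allocated equally to four groups".

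The Statistical analysis section matches the five comparisons: "Repeated measures analysis of variance (RM ANOVA) with Bonferroni procedure to adjust for the five comparisons will be used".

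**The concern.** Two things do not fit.

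First, the step from 20 to 38 is attributed to five comparisons, but the printed formula with a five-fold Bonferroni correction does not give 38.

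Second, a size derived from the contrast expected to be largest is offered as the size for five contrasts. A correction of alpha deals with the number of tests. It does not deal with the smaller differences that some of those tests must face.

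At stake is how the four-arm design will be read. The article presents the factorial layout as the means to assess individual, complementary or synergistic effects. Those conclusions rest on the four contrasts for which no difference was assumed. A reader told that the trial was sized for five comparisons could take a non-significant result in one of them as evidence that an agent does nothing, or that the combination adds nothing.

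**Working it through.** **Inputs.** From Sample size: means 86.8 and 94.6, SDs 6.40 and 10.30, two-sided alpha 0.05 (the formula uses Z at 1 − α/2), type II error 0.20, 38 per group, 10% attrition. From Statistical analysis: Bonferroni for five comparisons, so alpha = 0.05/5 = 0.01.

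**Formula in the plan.** n = (Z₁₋α/₂ + Z₁₋β)² (S₁² + S₂²) / (μ₁ − μ₂)²
- S₁² + S₂² = 40.96 + 106.09 = 147.05
- (μ₁ − μ₂)² = 7.8² = 60.84
- SD per arm for power = √(147.05/2) = 8.575

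**Reproducing the plan's figures**
- Base size: (1.960 + 0.842)² × 147.05/60.84 = 18.97, so 19, or 20 with the t distribution. The stated 20 reproduces.
- Total: 38 × 4 = 152, and 152 × 1.1 = 167.2, so 168. The stated total reproduces from 38.
- Adjusted size: (2.576 + 0.842)² × 147.05/60.84 = 28.2, so 29 (t-based 30). The stated 38 does not reproduce.

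**Routes that do reach 38.** None is stated for this step.
- Twice the unrounded base size: 2 × 18.97 = 37.9.
- Alpha 0.01 with 90% power, t-based: 38.
- 80% power with alpha 0.05/25 = 0.002: 37.4, so 38.

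**Why one difference cannot serve all five.** For either single agent,

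(placebo − agent) + (agent − combination) = placebo − combination = 7.8.

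If the agent's mean lies between the other two, both terms are non-negative and the smaller is at most 7.8/2 = 3.9. This applies once for vitamin D and once for omega-3, so at least two of the other four contrasts have a difference of 3.9 or less.

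**Power at 38 per group, two-sided alpha 0.01, SD 8.575, end values.** The standard error is 8.575 × √(2/38) = 1.967.

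| Difference | Difference / SE | Power, t | Power, normal |
|---|---|---|---|
| 7.8 | 3.97 | 90% | 92% |
| 3.9 | 1.98 | 26% | 28% |
| 2.6 | 1.32 | 10% | 10% |

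- Smallest difference with 80% power: (2.576 + 0.842) × 1.967 = 6.7.
- Size for 80% power at 3.9: (2.576 + 0.842)² × 147.05/3.9² = 112.9, so 113 per group.

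**Range for a difference of 3.9 under assumptions the article does not fix**

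| Assumption | Power |
|---|---|
| Common SD 10.3, end values | 17-18% |
| Common SD 6.4, end values | 51-53% |
| Change score, correlation 0.5 | about 26% |
| Change score, correlation 0.7 | about 47% |
| Change score, correlation 0.8 | about 69% |

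The change-score rows use SD × √(2(1 − r)) and the t distribution, where r is the correlation between baseline and eight weeks. The article gives no value for r, so these values are assumptions.

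**The case against.** The other side has real force on several points.

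- **80% power for each comparison is never stated.** The 20% type II error is attached to the base calculation of 20 per group, and the increase to 38 is described only as a multiplicity adjustment. This stands: the claim is implied, because no other error rate or difference is offered for the five comparisons.
- **A reader might infer that 7.8 can hold only for combination versus placebo.** The documents do not support that. A single agent could also differ from placebo by 7.8, in which case the combination adds nothing to it. What is excluded is 7.8 in all five.
- **A reader might infer that all four other contrasts are weak.** That does not follow either. With a split of 5.0 and 2.8, power is about 46-49% for one and 12% for the other. With 7.8 and 0, one contrast has about 90%. The identity weakens at least one contrast per agent.
- **The bound on power needs the agent's mean to lie between placebo and combination.** The tests are two-sided, so an agent 7.0 worse than placebo and 14.8 worse than the combination would be detected in both. That pattern is improbable, but the condition has to be stated.
- **The primary outcome is change from baseline.** A high correlation would raise power, and about 0.83 to 0.84 would bring 3.9 to 80%. However, the plan's formula uses end-value SDs and no correlation, so the article cannot claim this gain.
- **38 exceeds 29.** A reader might infer that the trial is too small for its main contrast, or that 38 is impossible. Neither holds. The figure is conservative for combination versus placebo, and its derivation is untraced. The analysis section also mentions correction for multiple endpoints, but the Sample size section gives only the five comparisons as its reason.

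**Conclusion.** The point holds in this form: the Sample size section justifies the trial for combination versus placebo only, yet presents 38 per group as the size for five comparisons, and 38 does not follow from the stated formula and inputs.

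For combination versus placebo there is no shortfall: 29 per group would suffice at alpha 0.01, and 38 gives about 90% power. For at least two of the other four contrasts, power is about 26-28% or less, given end values, the plan's SDs, alpha 0.01 and single-agent means between placebo and combination. Across the SDs and correlations tried, power at 3.9 runs from 17% to about 71%, so no setting reaches the implied 80%. A correlation above those tried could reach it, but the article gives no basis for assuming one.

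**What to change.** Keep the sample size and correct the paragraph.

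1. Say that the formula gives 29 per group for combination versus placebo at alpha 0.01 and 80% power, and that 38 gives about 90% power for a difference of 7.8. Alternatively, state the rule that actually produced 38.
2. State that the size is justified for combination versus placebo only.
3. Give the smallest detectable difference at 38 per group (6.7 at 80% power, alpha 0.01, end values) and the power of the other four contrasts under stated differences and SDs. If change scores are relied on, state the assumed correlation.
4. Report those four contrasts with confidence intervals, and say that non-significance in them will not be read as absence of effect.

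The cost is protocol wording and no extra participants. The downside is that the stated power becomes less favourable for at least two of the five comparisons.
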